#### Secondary objectives

The secondary objectives are, first, to assess whether generalist treatment (GIT-PD) is non-inferior (*d* ≥ − 0.25) to specialist treatment (MBT/ST) in improving general symptom severity and psychosocial functioning in participants with severe personality disorders from baseline to the end of treatment (18 months; T4). Second, to evaluate whether generalist treatment (GIT-PD) is non-inferior to specialist treatment (MBT/ST) in participants with severe personality disorders in maintaining improvements observed at 18 months in personality functioning, general symptom severity, and psychosocial functioning from baseline to 12-month follow-up (30 months; T6). Third, to determine whether generalist treatment (GIT-PD) is more cost-effective than specialist treatment (MBT/ST) in terms of improvements in personality functioning for participants with severe personality disorders. Fourth, to explore the extent to which an algorithmically optimised combination of demographic, clinical, and psychosocial variables can predict differential treatment response (as measured by change in level of personality functioning (LPF) between baseline and end of treatment) between generalist (GIT-PD) and specialist (MBT/ST) treatments, with the expectation that combining predictors in one algorithm will outperform chance-level prediction.

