*Personalised Advantage Index*. In examining what treatment works better for whom, an algorithm will be built that predicts differential treatment responses regarding LPF between generalist and specialist treatment. The algorithm quantifies the magnitude by which either treatment is estimated to outperform the other on the participant level, using the Personalised Advantage Index (PAI). The PAI was initially developed by DeRubeis et al. [44], but recently Meinke et al. [124] revised the algorithm, addressing key analytical issues in the traditional approach. As a result, this Advanced PAI approach introduced less risk of bias and prevented data leakage, thus providing more precise estimates while minimising the risk of overestimating model performance. Following Meinke et al.’s [124] guidance, PAI analyses will be conducted using their open-source code. This means a 5-fold cross-validation with 100 iterations will be utilised, covering not only the data preprocessing steps in terms of candidate predictor exclusion, imputation, and selection but also training, testing, and evaluating the performance of the models. More specifically, candidate predictors will be excluded if more than 30% of values are missing, while imputing missing values for the remaining candidate predictors. Herein, the mode will be used for categorical and binary variables, while multivariate imputation by chained equations (MICE) is going to be used for numerical variables. Furthermore, predictors lacking variance and binary predictors with 90% of participants or more in either category will be excluded. Multicollinearity between candidate predictors is operationalised as Pearson correlation (numerical variables) or Jaccard similarity (binary variables) of  > 0.75. Either of two similar candidate predictors should be removed by excluding the variable with the highest mean correlation/similarity with the remaining predictors. Candidate predictor exclusion will be repeated until no correlation/similarity of  > 0.75 is observed.

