Subsequently, distinct prediction models are to be fitted for the generalist and specialist treatment. First, predictors will be selected using Elastic Net regression, which is a supervised machine-learning method that combines the penalised linear Lasso and Ridge regressions to identify a parsimonious and stable subset of predictors. Then, Ridge regression will be used to fit the final prediction models using the selected predictors per treatment. For the participants in the test-fold of the 5-fold cross-validation, the resulting prediction models will be used to calculate a ‘factual’ prediction for the treatment actually received and a ‘counterfactual’ prediction for the treatment not actually received. To quantify the performance of the prediction models for both treatments, the outcome of the factual prediction will be compared to the actual LPF at post-treatment in terms of the mean absolute error (MAE), the root mean square error (RMSE), and the correlation.

The PAI scores are then derived from subtracting the counterfactual prediction from the factual prediction to discern whether a participant received their optimal or non-optimal treatment. Negative and positive PAI scores refer to having received the optimal and nonoptimal treatment, respectively. The PAIs utility in guiding treatment selection will be evaluated through comparing LPF at post-treatment for participants having received their optimal versus nonoptimal treatment using an independent one-sided t-test. Additionally, Cohen’s *d* will be computed for the mean difference. As per customary practice in PAI analyses, this evaluation should be repeated for the 50% of participants with the largest absolute PAI scores to determine utility for those with the strongest predictions. The Advanced PAI approach will be performed for both the clinician-rated (STiP-5.1) and the self-reported LPF (LPFS-BF 2.0).

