#### Methods for any additional analyses (e.g. subgroup and sensitivity analyses) {27d}

N/A. Other than the above-mentioned (sensitivity) analyses, no additional analyses are planned.

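### The t-test that judges the Personalised Advantage Index mixes the average arm difference with differential response, so it can come out positive when no patient characteristic moderates the effect

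*Protocol article*

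**What the plan says.** The fourth secondary objective (Protocol article, Secondary objectives) is to explore how well combined baseline variables predict differential response between generalist and specialist treatment, "with the expectation that combining predictors in one algorithm will outperform chance-level prediction".

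The method is in Statistical methods {27a}, under Personalised Advantage Index:

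- "distinct prediction models are to be fitted for the generalist and specialist treatment", using elastic-net selection followed by ridge regression; "a 5-fold cross-validation with 100 iterations will be utilised".
- The PAI is the prediction for the treatment received minus the prediction for the other treatment. "Negative and positive PAI scores refer to having received the optimal and nonoptimal treatment, respectively".
- For model performance, "the outcome of the factual prediction will be compared to the actual LPF at post-treatment", by mean absolute error, root mean square error and correlation.
- Utility is assessed by "comparing LPF at post-treatment for participants having received their optimal versus nonoptimal treatment using an independent one-sided t-test", with Cohen's d.
- As a second look, "this evaluation should be repeated for the 50% of participants with the largest absolute PAI scores".

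No significance level is given for this t-test. The section on additional analyses {27d} adds: "Other than the above-mentioned (sensitivity) analyses, no additional analyses are planned".

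**The concern.** Each arm's model carries that arm's mean outcome. If one treatment is better by the same amount for everyone, the PAI scores tilt towards it. Most participants in the better arm are then labelled optimal and most in the worse arm nonoptimal. A pooled t-test with no arm term partly compares the arms again, and a significant result says little about who benefits from which treatment.

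Nothing else stated in the plan separates the two explanations. The accuracy measures concern only the treatment received, so they show prognostic and not differential prediction. The top-half analysis repeats the same test. Cross-validation limits overfitting but leaves the arm difference in place.

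The Discussion ties this objective to the allocation of scarce specialist care. A positive result could support an algorithm that does no better than assigning everyone to one arm.

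**Working it through.** **Inputs from the plan.** Sample size {19} gives 316 evaluable participants, 158 per arm, inflated to 316/0.883 = 357.87, hence 358. The 316 comes from the authors' own simulation. A closed form for the linear time-by-treatment slope over seven equally spaced visits with correlation 0.50 has variance 36 × 0.5/28 = 0.643. With margin 0.25, one-sided 0.025 and power 0.80 it gives 162 per arm, 324 in total, within 3% of 316. The plan states no operating characteristic for the PAI t-test, so there is no figure to reproduce for that.

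**Step 1: where the arm difference enters.** Assume no moderation, with higher scores worse and one arm worse by d for everyone. Write the fitted models as an arm mean plus a predictor part. In the better arm,

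PAI = (mean_better − mean_worse) + (difference in fitted predictor parts) ≈ −d + noise.

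In the worse arm, PAI ≈ +d + noise. The sign therefore follows the arm, blurred only by estimation noise.

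**Step 2: limiting case.** If every PAI favours the better arm, the test is exactly better arm against worse arm. With unit SD,

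P(significant) = Φ(d × √(158/2) − z).

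At d = 0.20 and one-sided 0.05: 0.20 × 8.89 = 1.78; 1.78 − 1.645 = 0.13; Φ = 0.55. At d = 0.25: 2.22 − 1.645 = 0.58; Φ = 0.72. At one-sided 0.025 the values are 0.43 and 0.60. These are the values when labels and arms coincide completely; the real pipeline falls short of that.

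**Step 3: the planned pipeline, no moderation.** Assumptions: 316 participants, 25 baseline predictors with prognostic effects only, elastic-net selection and ridge per arm, 5-fold cross-validation averaged over 5 repeats, 600 simulated trials per row.

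| d | Share sent to better arm | t-test, 0.05 | t-test, 0.025 | Top half, 0.05 | Interaction test, 0.05 | Mean apparent d |
|---|---|---|---|---|---|---|
| 0 | 0.51 | 9% | 5% | 10% | 7% | 0.01 |
| 0.10 | 0.63 | 14% | 9% | 13% | 7% | 0.03 |
| 0.20 | 0.72 | 21% | 16% | 19% | 5% | 0.08 |
| 0.25 | 0.78 | 40% | 30% | 34% | 8% | 0.15 |
| 0.30 | 0.82 | 53% | 43% | 46% | 7% | 0.19 |
| 0.50 | 0.93 | 95% | 92% | 86% | 5% | 0.43 |

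Simulation error is about √(0.4 × 0.6/600) = 2 percentage points at 40% and 1 point near 9%. A second simulation, also with elastic-net selection, gave 8% (5% at one-sided 0.025) at d = 0, 22% (16%) at 0.20, 35% (26%) at 0.25 and 72% (66%) at 0.40. Its interaction test stayed at 5–7%.

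**Step 4: does arm composition explain the apparent effect?** If a share q of recommendations goes to the better arm, a fraction q of the optimal group comes from the better arm and a fraction q of the nonoptimal group from the worse arm. The expected difference is then d(2q − 1). At d = 0.25: 0.25 × (2 × 0.781 − 1) = 0.14, against 0.15 simulated. At d = 0.50: 0.50 × (2 × 0.93 − 1) = 0.43, against 0.43. The arm difference accounts for essentially all of the apparent benefit.

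**Step 5: does the alternative keep power?** With true moderation (assumed 0.5 SD difference in slope) and d = 0, the interaction test rejected in 87% and the t-test in 83%. In the second simulation, under true moderation, the figures were 79% and 69%.

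**The case against.** The objective is exploratory and fourth among the secondary ones, and the question asked is which characteristics matter, which one p-value does not settle. The sample size assumes equal improvement in both arms, and at d = 0 the excess is small: 8–9% against 5%, or about 5% against 2.5%. No alpha is stated for this test, so 0.05 is an assumption. With a large arm difference, the primary analysis would itself alert the reader. The plan follows cited open-source code that is not shown and may report further comparisons. All of this stands and limits the weight of the point. It does not remove it, because the article names this t-test as the means of evaluating utility.

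Three stronger readings are tempting and are not supported:

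- **That false positives typically run far higher.** Simulations with ridge alone gave 28–39% at d = 0.20, 38–57% at d = 0.25 and 82–93% at d = 0.40, all at one-sided 0.05. They omit the elastic-net step that the plan specifies, and d = 0.40 lies beyond the margin.
- **That cross-validated labels separately invalidate the t-test through dependence.** This was not isolated. When observed arm means were removed before fitting, rejection at d = 0 fell from 9.4% to 5.2% in one setting but only from 8.6% to 7.8% in another. Much of the excess can come from the chance arm difference choosing the direction of a one-sided test.
- **That the non-inferiority result is compromised.** It rests on a different model and does not use the PAI.

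**Conclusion.** The point holds as a defect in the stated criterion: the pooled t-test does not isolate differential response. Its structure follows from the plan's own text. Its size depends on the true average arm difference, being modest at d = 0 to 0.10 and substantial from about d = 0.20. With no moderation the range is 21–22% at d = 0.20 and 35–40% at d = 0.25 at one-sided 0.05, or about 16% and 26–30% at one-sided 0.025.

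Differences of this size are plausible here. The margin tolerates a generalist deficit approaching 0.25, a non-inferiority finding leaves generalist superiority open, and a failed one leaves inferiority open.

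The exact rates rest on assumed alpha, predictor number and strength, penalties, and few cross-validation repeats in place of 100 iterations. The correction is worth making before analysis; the primary conclusion does not depend on it.

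**What to change.** 1. Make the utility test the interaction between assigned arm and cross-validated predicted advantage, D = specialist prediction minus generalist prediction. Fit outcome = b0 + b1 × arm + b2 × D + b3 × arm × D, with arm = 1 for generalist. The average arm difference goes into b1. As higher scores are worse, a useful PAI implies b3 < 0. State the alpha.
2. Report the estimated mean outcome under PAI allocation against giving everyone the better single arm.
3. Keep the optimal/nonoptimal t-test and Cohen's d, including the top-half repeat, as descriptive.

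The interaction test is not perfectly calibrated (5–8% at a nominal 5% in these simulations), but it does not drift with the arm difference. Permuting predictor rows within arm to obtain a p-value is not advised: it also destroys prognostic associations, so it tests whether the predictors are unrelated to outcome and not whether moderation is absent.

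The cost is a little more analysis work and revised wording, with no new data. Fewer positive PAI results should be expected when the arms differ on average.

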The secondary outcomes, among others, include the mean differences in change from baseline to the end of treatment (T4) in symptom severity (SIPP-SF, SCID-5-PQ, BSI, C-SSRS; for an outline of the here-abbreviated outcome measures, see *Plans for assessment and collection of trial data {25a})* and psychosocial functioning (WHODAS 2.0, EQ-5D-5 L, Q-LES-Q-SF) between the generalist (GIT-PD) and specialist treatment (MBT/ST) conditions. Additional secondary outcomes assess the mean differences in change from baseline to follow-up (T6) between the generalist (GIT-PD) and specialist treatment (MBT/ST) conditions in personality functioning (STiP-5.1, LPFS-BF 2.0), symptom severity (SIPP-SF, SCID-5-PQ, BSI, C-SSRS), and psychosocial functioning (WHODAS 2.0, EQ-5D-5 L, Q-LES-Q-SF). For both the short- and long-term outcomes, all available measurement points are included in the model. The secondary outcome surrounding cost-effectiveness and cost-utility of generalist (GIT-PD) versus specialist treatment (MBT/ST) addresses the incremental effects set off against the incremental costs from baseline to end of treatment (T4), calculating an incremental cost-effectiveness ratio (ICER). For the cost-effectiveness analysis, improvement in personality functioning (STiP-5.1, LPFS-BF 2.0) is set off against the incremental costs, referring to direct and indirect costs, such as treatment costs (electronic patient file data), further healthcare consumption and productivity loss (TiC-P). All the while, cost-utility is measured in quality-adjusted life years (QALYs) gained throughout the assigned intervention, calculated from EQ-5D-5L scores. The final secondary outcome measures the combined predictive value of end-of-treatment differential treatment response, based on several pre-randomisation variables. The predictive value is expressed in a personal advantage score in terms of LPF improvement from baseline (STiP-5.1, LPFS-BF 2.0). The pre-randomisation variables with prescriptive and/or prognostic value are selected and used for predicting advantage scores through the development of a PAI algorithm. For a detailed description of the instruments and the timeline of assessment, see *Plans for assessment and collection of outcomes {25a}* and *Participant timeline {18}*.

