### Sample size {19}

The required sample size was determined using a computer simulation. Twenty-one thousand datasets with varying sample sizes were simulated for an RCT design with seven repeated measurements on a continuous outcome variable, where both interventions exhibit equal improvement over time. The outcome measures were assumed to follow a multivariate normal distribution in both groups, with a repeated measures correlation of 0.50 and a decrease of *d* = 0.30 in both groups across the seven repeated measurements. Each of these datasets was analysed using a longitudinal multilevel model (see *Statistical methods for primary and secondary outcomes, including harms {27a}).* Subsequently, in each dataset, it was tested whether generalist treatment is non-inferior to specialist treatment by examining whether the lower limit of the two-sided 95% confidence interval of the difference between treatments in improvement over time is greater than the non-inferiority limit of *d* = 0.25. It was found that with this design, 316 participants are necessary (158 per group) to test non-inferiority with a power of 0.80 and α = 0.025. To account for attrition, which we estimate at 11.7% for the primary endpoint (T4) based on a similar study [19], the complete sample needs to consist of (316/0.883 = 357.87) 358 participants. This comes down to 179 participants per treatment condition.

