#### Predictors

The aforementioned secondary instruments assessed at baseline will also serve as candidate predictors in the PAI analysis. These candidate predictors have been selected based on previously identified predictors in comparable analyses [45, 82], as well as alignment with variables examined in ongoing or upcoming trials on optimal treatment selection for personality disorders [83–86]. Moreover, their inclusion allows for replication and verification of related findings, enhancing the robustness of predictor research surrounding PD.

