### Statistical methods

#### Statistical methods for primary and secondary outcomes including harms {27a}

*Non-inferiority.* The primary research question is answered through longitudinal multilevel modelling of the short-term difference (T4; 18 months) between generalist (GIT-PD) and specialist treatment (MBT/ST) in improvement of personality functioning, following the intention-to-treat principle. Two separate multilevel mixed-effects models are used for the two primary outcomes, meaning both the STiP-5.1 at two time points and the LPFS-BF 2.0 at five time points. The model levels refer to the repeated measurements (level 1) of each individual (level 2) nested within treatment sites (level 3). Both models will be adjusted for the respective baseline outcome value, while random intercepts and slopes are modelled to account for the heterogeneous individual change trajectories over time. Furthermore, random intercepts and slopes are modelled on the treatment site level to account for heterogeneous change trajectories across sites. No further covariates will be added. Two-tailed significance levels are set at *α* = 0.05, while effect estimates are reported with corresponding 95% two-sided confidence intervals. If the required sample size is not achieved due to problems with enrolment and inclusion, all non-inferiority analyses are converted to a one-sided confidence interval approach in order to retain sufficient statistical power. In case of convergence issues, the model’s complexity will be reduced by 1) not modelling the random slope but only the random intercept at the third level of treatment site, 2) replacing treatment site with institution with regards to the third level along with the respective random intercepts and slopes, or 3) omitting the third level in the analysis altogether if necessary. Trial-level non-inferiority will be assessed using a fixed-sequence testing procedure [117], prioritising the clinician-rated LPF (STiP-5.1) due to its blinded assessment and superior capability of measuring latent PD severity [58, 59]. If non-inferiority is demonstrated on the STiP-5.1, the self-reported LPFS-BF 2.0 will be tested subsequently to provide additional supportive evidence, given its high sensitivity to change [60]. If non-inferiority is not demonstrated on the STiP-5.1, the LPFS-BF 2.0 will not be formally tested as a primary outcome, and non-inferiority cannot be concluded at the trial level. This hierarchical approach preserves statistical power while controlling the family-wise error rate across multiple endpoints and prioritising blinded assessment to minimise potential bias.

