
To answer the secondary research questions regarding long-term (T6; 30 months) non-inferiority of generalist (GIT-PD) versus specialist treatment (MBT/ST) in improving personality functioning, an identical intention-to-treat longitudinal multilevel model will be fit as for the primary outcome, while including all available repeated measures. This ultimately results in the inclusion of three and seven repeated measures for the STiP-5.1 and LPFS-BF 2.0, respectively. Likewise, to assess the short-term (T4; 18 months), as well as the long-term (T6; 30 months) non-inferiority of generalist (GIT-PD) versus specialist treatment (MBT/ST) in improving symptom severity and psychosocial functioning, the same intention-to-treat longitudinal multilevel model will be applied for each of the secondary study parameters (SIPP-SF, SCID-5-PQ, BSI, C-SSRS, WHODAS 2.0, EQ-5D-5 L, Q-LES-Q-SF). Likewise, for the short-term outcome, the five repeated measures (level 1) of each individual (level 2) are nested within treatment sites (level 3). Models are adjusted for the respective outcome’s baseline value, random intercepts, and slopes are modelled at the second and third level to account for heterogeneous individual and treatment site change trajectories over time, and two-tailed significance levels are set at *α* = 0.05, while effect estimates are reported with corresponding 95% two-sided confidence intervals. The non-inferiority margin is set at *d* = − 0.25. On top of that, all AEs and SAEs are descriptively reported for both treatment arms.

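### The PAI utility test compares post-treatment personality functioning without baseline adjustment: unbiased, but less precise than the data allow and out of line with the plan's own definition of response

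*Protocol article*

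**What the plan says.** In the protocol article, Statistical methods {27a}, the PAI paragraphs label each participant as having received the predicted-optimal or nonoptimal treatment. Utility is then evaluated by "comparing LPF at post-treatment for participants having received their optimal versus nonoptimal treatment using an independent one-sided t-test", with Cohen's d for the mean difference. The plan adds that "this evaluation should be repeated for the 50% of participants with the largest absolute PAI scores". Both steps are run for the STiP-5.1 and the LPFS-BF 2.0.

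The same section treats baseline differently elsewhere. For the two primary outcomes, "Both models will be adjusted for the respective baseline outcome value". For the secondary outcomes, "Models are adjusted for the respective outcome’s baseline value".

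The PAI question is posed in terms of change. Secondary objectives defines differential response "as measured by change in level of personality functioning (LPF) between baseline and end of treatment", and Outcomes {16} likewise expresses the advantage score as improvement in personality functioning since baseline. The evaluation step uses the post-treatment score alone.

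**The concern.** Every participant has a baseline score on the instrument used as the outcome of the PAI evaluation. Leaving it out keeps differences in starting severity between patients as noise in the comparison. The loss weighs most in the half of the sample with the strongest predictions, where numbers are halved.

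This affects one of the three main questions in the Abstract: which patients do better with which treatment. The trial was sized for non-inferiority, and the article states no power for the PAI comparison, so there is no evident precision to spare. There is also a mismatch of wording: the objective and the outcome definition speak of change or improvement from baseline, while the test is on a raw end score.

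**Working it through.** **Inputs from the protocol article**
- Test: independent one-sided t-test on post-treatment score, no covariate (Statistical methods {27a}).
- Correlation: the sample size simulation was run "with a repeated measures correlation of 0.50" (Sample size {19}).
- Evaluable participants: 316, or 158 per randomised arm; attrition 11.7%; total 358 (Sample size {19}).
- Allocation 1:1 (Method of sequence generation {21b}); randomisation after the baseline measurements (Implementation {23}).

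**Assumptions, not in the article:** one-sided 5% level for the PAI test, effect sizes of 0.25 and 0.30, an even optimal/nonoptimal split, and one test with fixed labels.

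**The plan's own figures.** 316/0.883 = 357.87, so 358, as stated. The 316 comes from a simulation. An analytic approximation uses a linear slope over seven equally spaced measurements with correlation 0.50. Its variance factor is 36 × 0.50/28 = 0.643, which gives 162 per group (324 in total), close to the stated 316. No figure is given for the PAI test, so there is none to reproduce.

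**Variance with and without baseline.** With outcome SD 1 and m per group:
- raw variance of the difference = 2/m
- adjusted variance = 2(1 − r²)/m
- ratio = 1 − r²

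| r | variance ratio | variance cut | SE ratio |
|---|---|---|---|
| 0.3 | 0.91 | 9% | 0.954 |
| 0.4 | 0.84 | 16% | 0.917 |
| 0.5 | 0.75 | 25% | 0.866 |
| 0.6 | 0.64 | 36% | 0.800 |

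At r = 0.50 the standard error falls by 13.4%. A raw comparison would need 316/0.75, about 422 participants, to match the adjusted analysis of 316.

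A simulation of 4,000 trials (N = 316, 1:1, r = 0.50, true difference −0.30) gave mean estimates of −0.302 raw and −0.303 adjusted, so neither is biased. The variance ratio was 0.775, against 0.75 in theory.

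**Illustrative power** = Φ(d/SE − 1.645)
- 158 v 158, d = 0.25, raw: SE = √(2/158) = 0.1125; Φ(2.222 − 1.645) = 0.72.
- Adjusted, r = 0.50: SE = √(1.5/158) = 0.0974; Φ(2.566 − 1.645) = 0.82.
- Adjusted, r = 0.3: SE = √(1.82/158) = 0.1073; Φ(2.329 − 1.645) = 0.75.
- 79 v 79 (the 50% subset), d = 0.30, raw: SE = 0.1591; Φ(1.886 − 1.645) = 0.60.
- Adjusted, r = 0.50: SE = 0.1378; Φ(2.177 − 1.645) = 0.70.

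**A change score is not a substitute.** Its variance is 2(1 − r), which is 1.00 at r = 0.50, the same as the raw post-treatment score. Moving to change would match the objective's wording but recover no precision at that correlation.

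**The case against.** The strongest reply is that this is a preference for efficiency, not an error. Under 1:1 allocation each participant has about a one-half chance of having received the predicted-optimal treatment, whatever the baseline score. The raw comparison is therefore unbiased, and chance imbalance is ordinary sampling error already reflected in its standard error. The objective is described as exploratory. This stands, and it limits the weight of the point.

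A reader might infer from the missing covariate that the PAI result would be biased, or that the non-inferiority conclusion is weakened. The documents support neither: randomisation protects the comparison, and the primary models adjust for baseline. Nor would confidence intervals be a quarter wider. The 25% is a reduction in variance; the standard error falls by about 13%.

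Second, the plan follows published PAI guidance and its open-source code, and keeping the customary test helps comparison with earlier work. That is a reason to keep the raw result alongside, not a reason to omit the adjusted one.

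Third, the size is uncertain. The 0.50 is a generic planning value, not an estimate for either instrument, and selecting participants on STiP-5.1 severity could lower it for that instrument. The power figures also ignore the 5-fold cross-validation with 100 iterations. Both objections stand, so a range is given and the powers are illustrations.

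It may also be said that baseline can enter as a candidate predictor. The Predictors section says that "The aforementioned secondary instruments assessed at baseline will also serve as candidate predictors in the PAI analysis" and does not name the baseline primary instruments there. Adding them would change the labels only; the t-test would remain unadjusted.

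Finally, the scores readministered before treatment (T0p) lie closer to treatment start after a long wait. They are collected after randomisation, however, and only when the wait is long enough, so the pre-randomisation baseline (T0b) is the safer covariate.

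**Conclusion.** The point holds as a modest, nearly free improvement. The article fixes an unadjusted test where its other outcome models adjust for baseline, and it tests a post-treatment score where its objective and outcome definition speak of change or improvement. The consequence is lost efficiency: 25% in variance at the plan's correlation of 0.50, with a range of 9% at 0.3 to 36% at 0.6. Under the stated assumptions that is worth about ten percentage points of power at 0.50, but only about three (0.72 to 0.75) at 0.3. The size rests on a planning correlation and on a level, effect sizes and split that the article does not give for this test.

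**What to change.** In the PAI part of Statistical methods {27a}, replace the t-test by a linear model of post-treatment score on the optimal/nonoptimal indicator, with the pre-randomisation baseline (T0b) score of the same instrument as covariate. Use it in the full sample and in the 50% with the largest absolute PAI scores, for the STiP-5.1 and the LPFS-BF 2.0.

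Report the adjusted mean difference and a Cohen's d standardised by the unadjusted outcome SD. Dividing by the residual SD would inflate d by 1/√0.75 = 1.155, about 15% at a correlation of 0.50, and break comparability with earlier PAI work. Keep the raw comparison as a supplementary result.

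At the same time, reconcile the outcome used here with Secondary objectives and Outcomes {16}, so that all three name the same quantity.

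The cost is a sentence or two in the plan, one covariate in the evaluation script and a small departure from the published code. No new data are needed.
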